#### Blinding

Blinding procedures will be implemented for study participants, efficacy evaluators, and statistical analysts. Given the inherent characteristics of acupuncture, there is no blindness for acupuncturists. The acupuncturists will not participate in any baseline assessment, randomization procedures, or outcome evaluation of the participants.

### Intervention

All acupuncture procedures will be performed by licensed acupuncturists possessing at least three years of clinical experience. Prior to the initiation of the trial, all participating acupuncturists will complete a comprehensive training program, which will focus on standard operating procedures for acupuncture, placebo acupuncture protocols. Detailed and quantifiable standardized operational procedures (SOPs) will be established for both the acupuncture and placebo acupuncture groups. These SOPs specified the acupoint localization methods, needling angle and depth, needle manipulation techniques, and needle retention time. Independent quality controllers will be designated to regularly assess acupuncturists’ adherence to the SOPs through on-site observation or video recording.

The acupuncture group will utilize sterile disposable needles (Hwato, Suzhou, China) of the following dimensions: 0.25×25 mm, 0.25×40 mm, and 0.30×75 mm. The placebo acupuncture group will receive non-penetrative placebo acupuncture using blunt-tipped needles (0.25×25 mm; Hwato, Suzhou, China), which are specifically engineered to mimic the tactile sensation of real needle insertion while preventing actual skin penetration. Both groups will utilize an adhesive circular pad with a diameter of 1 cm. This pad serves dual purposes: securing the placebo needle to the skin surface and facilitating the blinding process. Following standard skin disinfection, each acupoint will be covered with a sterile pad that directs the placebo needle to the skin surface. Depending on the group assignment as per the study protocol, the needle will either be inserted to a predetermined depth (acupuncture group) or remain on the skin surface without penetration (placebo acupuncture group).

#### Acupuncture group

For the acupuncture group, two sets of acupoints (Set 1 and Set 2) will be used: Set 1 and Set 2. Set 1 (administered in the supine position) includes the following points: CV12 (Zhongwan), KI16 (Huangshu), CV4 (Guanyuan), KI12 (Dahe), SP6 (Sanyinjiao), and LR3 (Taichong). Set 2 (administered in the prone position) consists of BL23 (Shenshu), BL33 (Zhongliao), and KI3 (Taixi). The two sets will be alternated, with Set 1 used for the initial treatment. Details regarding the anatomical locations of these acupoints and the specific manipulation techniques employed in the acupuncture group are presented in **Table 2**. All acupoint locations will be determined in compliance with the World Health Organization Standardized Acupuncture Points guidelines (14).

**Table 2 T2:** Location of acupoints and manipulation techniques used for Acupuncture group.

Acupoints	Location	Manipulation
Set 1 acupoints		
CV12 (Zhongwan)	On the anterior midline, 4 cun above the umbilicus	Inserted vertically to a depth of 1.0 cun–1.5 cun
KI16 (Huangshu)	Bilateral,0.5 cun lateral to the umbilicus	Inserted vertically to a depth of 1.0 cun–1.5 cun
CV4 (Guanyuan)	On the anterior midline, 3 cun below the umbilicus	Inserted vertically to a depth of 1.0 cun–1.5 cun
KI12 (Dahe)	Bilateral, 4 cun below the umbilicus, and 0.5 cun lateral to the lower anterior midline	Inserted vertically to a depth of 1.0 cun–1.5 cun
SP6 (Sanyinjiao)	Bilateral, posterior to the medial border of the tibia, and 3 cun above to the tip of the medial malleolus	Inserted vertically to a depth of 1.0 cun–1.5 cun
LR3 (Taichong)	Bilateral, in the depression anterior to the junction of the first and second metatarsal bones	Inserted vertically to a depth of 0.5 cun– 0.8 cun
Set 2 acupoints		
BL23 (Shenshu)	Bilateral, 1.5 cun lateral to the depression below the spinous of the second lumbar vertebra	Inserted vertically to a depth of 1.0 cun–1.5 cun
BL33 (Zhongliao)	Bilateral, in the sacral region, and precisely at the site of the third sacral posterior foramen	inserted bilaterally into the third posterior sacral foramina (at BL33) and angled inwards and downwards at 50–60° to a depth of 60–70 mm
KI3 (Taixi)	Bilateral, in the depression between the tip of the midial malleolus and the Achilles tendon	Inserted vertically to a depth of 0.5 cun–1.0 cun

1 cun (≈ 20 mm) is defned as the width of the interphalangeal joint of the participant’s thumb.

Participants will assume the appropriate body position corresponding to the designated set of acupoints. After disinfecting the skin, sterile adhesive pads will be positioned at each acupoint, through which acupuncture needles will be advanced into the skin. Following needle insertion, standardized manual techniques (lifting, thrusting, and twirling) will be applied to elicit deqi, a characteristic complex of needling sensations including soreness, numbness, distension, or heaviness considered essential for therapeutic efficacy (15). Each acupuncture session will last 20 minutes.

Acupuncture interventions will commence during the first two menstrual cycles preceding the IVF cycle and continue until the day of oocyte retrieval (**Figure 2**). Each participant will complete three sessions weekly (ideally spaced every other day) over roughly ten consecutive weeks, about 30 sessions. If menstruation occurs during the acupuncture treatment period, the acupuncture sessions will proceed as scheduled without interruption.

**Figure 2 f2:**
[figure not shown]
Diagram of acupuncture treatment course. M1, on the first day of the menstrual cycle; IVF, *in vitro* fertilization.

#### Placebo acupuncture group

For the placebo acupuncture group, two sets of acupoints (Set 1 and Set 2) will also be used. To reduce specific therapeutic responses, non-acupoint sham sites distant from established acupoints will be utilized, with detailed locations and stimulation parameters documented in **Table 3**. The selection of sham acupoints for the control group is based on the “non-meridian, non-acupoint” principle. Points are located on the body surface at least 1 cun (a traditional unit of measurement, about 20 mm) away from any true acupoint and not situated on a recognized meridian pathway. Moreover, a non-penetrating sham needle is used at these locations to further minimize physiological stimulation. This combined approach (employing both non-meridian, non-acupoint sites and a non-penetrating needle technique) has been reported previously (16) and is considered an effective method for blinding participants and reducing nonspecific therapeutic effects.

**Table 3 T3:** Location of points and manipulation techniques used for placebo acupuncture group.

Acupoints	Location	Manipulation
Set 1 acupoints		
Non-acupoint 1	On the anterior midline, 4 cun above the umbilicus, 1 cun to the left from CV12 (Zhongwan)	No skin penetration
Non-acupoint 2	Bilateral, 1.5 cun lateral to the umbilicus, 1 cun lateral to KI16(Huangshu)	No skin penetration
Non-acupoint 3	On the anterior midline, 3 cun below the umbilicus, 1 cun to the right from CV4 (Guanyuan)	No skin penetration
Non-acupoint 4	Bilateral, 4 cun below the umbilicus, and 1.5 cun lateral to the lower anterior midline, 1 cun lateral to KI12(Dahe)	No skin penetration
Non-acupoint 5	Bilateral, 3 cun above the tip of the medial malleolus between SP6 (Sanyinjiao) and Achilles tendon	No skin penetration
Non-acupoint 6	Bilateral, in the depression anterior to the junction of the second and third metatarsal bones	No skin penetration
Set 2 acupoints		
Non-acupoint 7	Bilateral, 0.75 cun lateral to BL23(Shenshu)	No skin penetration
Non-acupoint 8	Bilateral, 1 cun lateral to BL33(Zhongliao)	No skin penetration
Non-acupoint 9	Bilateral, on the inner side of the foot, behind the inner ankle, at the same level as KI3 (Taixi), at the anterior edge of the Achilles tendon	No skin penetration

1 cun (≈ 20 mm) is defned as the width of the interphalangeal joint of the participant’s thumb.

The two sets will be alternated, with Set 1 used as the initial treatment. Placebo acupuncture will be administered using blunt-tip placebo needles (Hwato, 0.25×25 mm) that prevent cutaneous penetration. Consistent with the acupuncture group, adhesive pads will initially be applied to the surface of placebo acupoints, and blunt-tipped pragmatic placebo needles will be placed on these pads. To minimize physiological effects, acupuncturists will follow standardized procedures for positioning blunt-tipped placebo needles on adhesive pads, maintaining light contact while avoiding any manipulative techniques. Placebo needles will be positioned superficially at control points using a non-penetrative technique that prevents actual skin puncture. The needle retention time and treatment course will be identical to the acupuncture group.

Throughout the trial, participants will receive isolated treatments to limit cross-communication and will be advised to refrain from concurrent relevant therapies. Any such additional treatments received will require documentation.

#### COH regimen

COH will be administered starting on menstrual cycle days 2–3 after pretreatment completion, utilizing either a GnRH antagonist protocol or microstimulation protocol in all enrolled participants. The administration of both GnRH antagonist and microstimulation protocols will be managed by certified reproductive endocrinology specialists across all trial sites. As some participants may meet the criteria for IVF initiation before concluding the full acupuncture pretreatment, this study will permit the initiation of COH cycles provided that patients have completed a minimum of 8 weeks of acupuncture pretreatment.

#### Permitted and prohibited concomitant treatments

To ensure unbiased evaluation of acupuncture outcomes, participants will be advised to avoid concomitant interventions such as traditional Chinese herbs, Chinese patent medicines, growth hormone preparations. Any form of acupuncture outside the experimental protocol will be prohibited.

### Outcome measurement

#### Primary outcome

The primary outcome is the CPR following the first fresh or frozen embryo transfer. Ultrasonographic identification of a gestational sac and fetal heartbeat at 28 days post-embryo transfer confirmed a clinical pregnancy. The CPR is defined as the proportion of clinical pregnancies to the total number of embryo transfer cycles.

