**Methods and analysis:**

This study is a multicenter, randomized, placebo-controlled trial conducted on a large scale. A total of 300 women with DOR preparing for IVF-ET will be randomized 1:1 to acupuncture or placebo acupuncture. Interventions will be administered from the second menstrual cycle preceding the IVF cycle until the day of oocyte retrieval. The primary outcome is the clinical pregnancy rate (CPR) following the first embryo transfer. Secondary outcomes include various IVF-ET indicators, such as the number of follicles ≥ 14 mm, estradiol (E2) levels, and endometrial thickness on the day of human chorionic gonadotropin (hCG) administration; the number of retrieved oocytes, metaphase II (MII) oocytes, and two pronuclei (2PN) fertilizations; as well as the rates of 2PN fertilization, available embryos, high-quality embryos, implantation, cycle cancellation, biochemical pregnancy, pregnancy loss, sustained pregnancy, and live birth. Additionally, ovarian reserve indicators—including antral follicle count (AFC), basal serum levels of follicle-stimulating hormone (FSH), luteinizing hormone (LH), and E2, and anti-Müllerian hormone (AMH)—along with scores from the Self-Rating Anxiety Scale (SAS) will also be evaluated.

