#### Randomization method

Randomization will be performed after obtaining informed consents. A secure online computerized randomization system will be utilized for randomization to ensure allocation concealment. This centralized web-based platform incorporates multiple functional modules for randomization, data entry, and management, and will be overseen by an independent statistical team. Qualified participants will be assigned to the acupuncyure or placebo acupuncyure groups in a 1:1 allocation ratio, employing stratified block randomization by age (< 35 years vs. ≥ 35 years) through a computer-generated system. Upon enrollment of eligible subjects, personnel responsible for randomization will log into the central randomization system via the internet to obtain a randomization number.

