#### Secondary outcomes

The secondary outcomes include the number of follicles ≥ 14 mm, E2 level, and endometrial thickness on the hCG trigger day; the number of retrieved oocytes, metaphase II (MII) oocytes, and two pronuclei (2PN) fertilizations; as well as the rates of 2PN fertilization, available embryos, high-quality embryos, implantation, cycle cancellation, biochemical pregnancy, pregnancy loss, sustained pregnancy, and live birth. The outcomes of IVF-ET and their definitions are summarized in **Table 4**. While the post-treatment observation will be terminated at about 24 weeks, data on live birth will be obtained through the participating centers’ mandatory, complete follow-up system extending to the end of pregnancy.

**Table 4 T4:** Diagnosis definitions of IVF-ET outcomes.

Diagnosis	Definition
Primary outcomes	
clinical pregnancy rate (CPR)	the number of clinical pregnancies divided by the total number of embryo transfer cycles.
Secondary outcomes	
Outcomes of IVF-ET	
2PN fertilization rate	the number of 2PN embryos divided by the number of MII oocytes
available embryo rate	the number of transferable embryos divided by the number of 2PN fertilization
high-quality embryo rate	the number of high-quality embryos divided by the number of normally fertilized cleavage embryos. High-quality embryos were defined based on the day of embryo transfer, according to the Istanbul consensus and Gardner criteria, as follows: Day 2: embryos with 4 cells, <10% fragmentation, and absence of multi-nucleation; Day 3: embryos with 8 cells, <10% fragmentation, and no multi-nucleation; Day 5: blastocysts at stage 4, with inner cell mass and trophectoderm both graded as A (17, 18).
Implantation rate	the number of gestational sacs divided by the number of embryos transferred.
cycle cancellation rate	the number of cancelled embryo transfer cycles divided by the number of embryo transfer cycles
biochemical pregnancy rate	the number of patients with positive serum b-hCG pregnancy test results divided by total embryo transfer cycles
pregnancy loss rate	the number of pregnancy termination cycles within 12 weeks divided by the number of embryo transfer cycles
sustained pregnancy rate	the number of cycles of pregnancy greater than 12 weeks divided by the number of embryo transfer cycles
live birth rate	the number of live births divided by total embryo transfer cycles.
Scale measurement	

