#### Sample size

Based on previous research (21, 22), we estimated that the CPR of IVF-ET in DOR patients after acupuncture pretreatment would be 38%, compared to 22% following placebo acupuncture pretreatment. A sample size of 120 participants per group has been determined to ensure 80% statistical power, with a two-sided alpha of 0.05. An initial total of 300 participants (150 per group) will be enrolled to allow for an anticipated 20% dropout rate.

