#### Statistical analysis

Analyses will be performed using SAS version 9.3 (SAS Institute Inc., Cary, NC, USA). The intention-to-treat (ITT) principle will be applied to all data analyses in this study. Multiple imputation will be employed to manage missing data. Continuous variables will be reported as mean ± standard deviation or median (interquartile range), and categorical variables as frequencies (percentages).

The primary outcome, CPR, was analyzed using multivariate logistic regression to calculate adjusted odds ratios (aORs) with 95% confidence intervals (CIs). The dependent variable in the model was clinical pregnancy (yes/no), and the independent variable was group allocation. The selection of covariates for adjustment was based on their established clinical relevance to IVF outcomes and any observed baseline imbalances between groups (p < 0.10). These covariates may include centers, age, baseline FSH level, AFC, COH protocol, number of retrieved oocytes, type of ET, number of embryos transferred, etc. Model fit was assessed using the Hosmer-Lemeshow test, and multicollinearity was evaluated via variance inflation factors. Additionally, a Per-Protocol (PP) analysis for priamry outcome will be performed as a sensitivity analysis. Other between-group comparisons will be performed using independent t-tests/Wilcoxon rank-sum tests for continuous data and chi-square/Fisher’s exact tests for categorical data, as appropriate. A two-sided *p* < 0.05 will define statistical significance.

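### The primary pregnancy rate is divided by embryo transfers, a count formed after randomisation, which conflicts with the stated intention-to-treat principle; how women without a transfer are counted is not stated

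*Protocol article*

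**What the plan says.** All references are to the protocol article.

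- **Outcome.** The Primary outcome section says "The primary outcome is the CPR following the first fresh or frozen embryo transfer" and then "The CPR is defined as the proportion of clinical pregnancies to the total number of embryo transfer cycles". Table 4 gives the same rate as "the number of clinical pregnancies divided by the total number of embryo transfer cycles".
- **Timing.** Under Randomization method: "Randomization will be performed after obtaining informed consents". The abstract adds: "Interventions will be administered from the second menstrual cycle preceding the IVF cycle until the day of oocyte retrieval". The Acupuncture group section puts this at roughly ten weeks.
- **Women without a transfer are foreseen.** Table 4 lists a cycle cancellation rate, "the number of cancelled embryo transfer cycles divided by the number of embryo transfer cycles", as a secondary outcome. No expected value is given.
- **Analysis.** The Statistical analysis section says "The intention-to-treat (ITT) principle will be applied to all data analyses in this study. Multiple imputation will be employed to manage missing data". The primary model is a logistic regression of clinical pregnancy (yes/no) on allocation. Its candidate covariates include the oocyte yield at retrieval, the kind of transfer and how many embryos were transferred.
- **Sample size.** The assumed rates are 38% and 22%, with 120 per group for 80% power at two-sided 0.05. Then: "An initial total of 300 participants (150 per group) will be enrolled to allow for an anticipated 20% dropout rate". The section does not say whether the rates are per transfer or per woman. Under the article's own definition CPR is per transfer, yet the section counts participants.

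**The concern.** Randomisation makes the two groups of women comparable at entry. It does not make the women who later reach a transfer comparable. Between randomisation and transfer lie the whole course of treatment, stimulation, retrieval, fertilisation and embryo culture. The secondary outcomes show that the trial expects treatment to act on these steps: oocytes retrieved, fertilisation, available embryos, cancellation. The women enrolled have fewer than five antral follicles and low AMH, so some may have nothing to transfer.

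A per-transfer rate leaves those women out of both numerator and denominator. If acupuncture brings more women with a poor prognosis to transfer, its per-transfer rate can fall while more of its women conceive. If fewer of its women reach transfer, the rate can rise with no gain per woman. The primary result would then not estimate the effect of being assigned to acupuncture, which is what the intention-to-treat statement promises.

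**Working it through.** **1. The statements side by side.** The outcome definition needs a transfer before a woman is counted. The analysis statement needs every randomised woman to be counted. They agree only if every randomised woman has a transfer (contradicted by the cancellation outcome) or if no transfer is coded as not pregnant (stated nowhere). Two candidate covariates, kind of transfer and number of embryos transferred, come from the transfer itself. Kind of transfer has no value without one, so a model that uses it either drops those women or imputes a value for an event that did not happen.

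**2. Direction of bias (transfer shares assumed).** Per-transfer rate = pregnancies / (women randomised × share with a transfer). Take 150 women and 30 pregnancies per arm, so 30/150 = 20% per woman in both.

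| Share with transfer, acupuncture / placebo | Per transfer, acupuncture | Per transfer, placebo | Odds ratio |
|---|---|---|---|
| 90% / 70% | 30/135 = 22.2% | 30/105 = 28.6% | 0.71 |
| 85% / 75% | 30/127.5 = 23.5% | 30/112.5 = 26.7% | 0.85 |
| 70% / 90% | 30/105 = 28.6% | 30/135 = 22.2% | 1.40 |

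With a pooled two-proportion test at two-sided 0.05, the per-transfer comparison rejects this true per-woman null about 9% of the time at 85/75 and about 20% at 90/70.

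A reversal is also possible. Suppose 70% of women reach transfer in either arm with a 30% pregnancy rate, and a further 10% reach it only with acupuncture, with a 10% rate.

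- Per woman: placebo 0.70 × 0.30 = 21%; acupuncture 0.21 + 0.10 × 0.10 = 22%.
- Per transfer: placebo 21/70 = 30.0%; acupuncture 22/80 = 27.5%.

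**3. The plan's sample size.** For 38% against 22%, 80% power and two-sided 0.05, the unpooled normal formula gives 125 per group and the pooled one 128; the plan states 120. Pooled power at 120 is 77.5%. The inflation is right: 120/(1 − 0.20) = 150. The gap between 120 and 125–128 is a small separate matter on which this point does not depend.

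**4. Power per woman.** Treat 38% and 22% as per-transfer rates and let q be the share without a transfer, equal in both arms (assumed). The per-woman rates are p₁ = 0.38(1 − q) and p₂ = 0.22(1 − q), with mean p̄. Then

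power = Φ{[(p₁ − p₂)√n − 1.96√(2p̄(1 − p̄))] / √(p₁(1 − p₁) + p₂(1 − p₂))}.

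For q = 10% and n = 150: [0.144 × 12.247 − 1.96 × √0.3942] / √0.3838 = 0.533/0.620 = 0.86, so power is 80.5%.

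| q | Per-woman rates | Power per woman, 150 per arm | Transfers per arm | Power per transfer | n per arm for 80%, per woman |
|---|---|---|---|---|---|
| 10% | 34.2% vs 19.8% | 80.5% | 135 | 82.2% | 149 |
| 20% | 30.4% vs 17.6% | 74.0% | 120 | 77.5% | 174 |
| 30% | 26.6% vs 15.4% | 66.5% | 105 | 71.9% | 207 |
| 40% | 22.8% vs 13.2% | 58.1% | 90 | 65.1% | 251 |

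The last column is before any inflation for dropout. Much of the loss arises under either denominator, because women without a transfer also shrink the per-transfer sample.

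**The case against.** The strongest reply is that the analysis may well be intention-to-treat in practice. The yes/no model can be run on all 300 women with no transfer coded as no, which fits the intention-to-treat sentence, and a condensed article may leave that coding to the analysis plan. This stands in part. A reader might infer that the primary analysis is certain to break intention-to-treat; the document does not settle that. What remains is that the outcome definition is not left open. It is given twice, with transfers as the denominator, and it conflicts with the analysis statement.

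A reader might also infer that imputation will assign pregnancies to women who had no embryo. The text does not limit imputation to women lost to follow-up, but neither does it say that a woman without a transfer is treated as missing. Any count of such pregnancies would rest on assumptions the document does not make.

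Finally, the first transfer may be fresh or frozen, so a woman whose fresh transfer is cancelled stays in the denominator if a frozen one follows. That reduces the number left out; it does not bring in women who never have a transfer. The shares used above are assumptions, and the reversal example is small (1 point per woman, 2.5 points per transfer) beside the planned 16-point difference.

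**Conclusion.** The concern holds as a contradiction in the plan: a primary rate defined per transfer, against an intention-to-treat principle declared for all analyses, with no rule for women who have no transfer. Followed as written, the definition can bias the comparison in either direction whenever transfer shares differ between arms. The illustrations show that this is possible and how it works. They do not show that it will be large here, because the document gives no transfer or cancellation rate. The power figures rest on three assumptions: that 38% and 22% are per transfer, that q is equal in both arms, and that all 150 women per arm are analysed. Because the conflict concerns the primary estimate, it should be resolved before analysis.

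**What to change.** - Define the primary outcome as clinical pregnancy after the first fresh or frozen transfer (yes/no) per woman randomised, within a stated follow-up window. Count no transfer in that window as not pregnant. The window is needed so that a woman still awaiting a frozen transfer has a defined outcome.
- Limit multiple imputation to women whose outcome is truly unknown.
- Remove kind of transfer, number of embryos transferred and other post-randomisation covariates, such as oocyte yield, from the primary model.
- Keep CPR per transfer as a secondary descriptive rate, and align the Primary outcome section and Table 4.
- Leave observed oocyte, MII and 2PN counts as recorded. Table 4 defines cancellation at the transfer, so a woman with a cancelled transfer may have real values for all three.
- State whether 38% and 22% are per transfer or per woman, and restate the power.

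The cost is a change of wording and model specification, with no new data. The downside is power: if the rates are per transfer, 150 per arm gives about 80% only when about 10% have no transfer, and 58% when 40% do not.

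### Pregnancy rates are defined per embryo transfer cycle without a limit to the first transfer: a wording mismatch for the primary outcome, a firmer gap for the secondary rates

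*Protocol article*

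**What the plan says.** In the Protocol article, the Primary outcome section opens: "The primary outcome is the CPR following the first fresh or frozen embryo transfer". After the ultrasound criterion, the same section gives the ratio: "The CPR is defined as the proportion of clinical pregnancies to the total number of embryo transfer cycles". Table 4 restates it, again without a limit to the first transfer: "the number of clinical pregnancies divided by the total number of embryo transfer cycles". The abstract and introduction both tie the primary outcome to the first transfer.

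The secondary rates in Table 4 carry no such limit:
- live birth is "the number of live births divided by total embryo transfer cycles";
- sustained pregnancy is "the number of cycles of pregnancy greater than 12 weeks divided by the number of embryo transfer cycles";
- biochemical pregnancy is "the number of patients with positive serum b-hCG pregnancy test results divided by total embryo transfer cycles";
- pregnancy loss is also per transfer cycle;
- implantation is gestational sacs per embryo transferred.

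Under Statistical analysis, the primary model is described thus: "The dependent variable in the model was clinical pregnancy (yes/no), and the independent variable was group allocation". Other between-group comparisons of categorical data use chi-square or Fisher's exact tests. The section also states: "The intention-to-treat (ITT) principle will be applied to all data analyses in this study".

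**The concern.** A first-transfer outcome gives at most one result per woman. A rate over all transfer cycles gives one result per cycle. The two differ as soon as any woman has a second transfer within the period that is counted.

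The women who add cycles are those whose first transfer failed and who still have embryos. The extra denominator is therefore selected after randomisation, on failure and on embryo yield, and embryo yield is itself something the trial measures as an outcome. Two cycles from one woman are correlated, and chi-square and Fisher's tests treat them as independent.

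If the primary outcome is taken on first transfers and live birth on all transfers, the two describe different sets of transfers. Live birth could then not be read as following the primary result through to delivery. The biochemical rate also puts patients over cycles, which is a proportion of one unit only if each woman has exactly one transfer.

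**Working it through.** **Can a second transfer fall inside observation?** Table 1 places the stimulation cycle at about week 10 and follow-up at week 24, and clinical pregnancy is read 28 days after transfer. A fresh transfer shortly after week 10 that fails is known at about week 15, which leaves roughly nine weeks in which a frozen transfer could take place. So it is possible. The article does not say that it happens or how often.

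**Inputs from the article (Sample size):** 38% against 22%, 120 women per group, two-sided alpha 0.05, 80% power, 20% dropout.

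**The plan's own figure.** The dropout step reproduces: 120/(1 − 0.20) = 150. The 120 does not quite reproduce. The usual formulas without continuity correction give 125 (unpooled variance) to 128 (pooled), and power at 120 is 77.5% (pooled). That is a separate matter, and nothing below rests on it.

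**Assumed inputs (not in the article):** a share *s* of women not pregnant after the first transfer has a second one, with success *f* times the first-transfer rate *p*.

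**Formula.** All-cycle rate = [p + (1 − p)·s·f·p] / [1 + (1 − p)·s].

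*Equal shares, s = 20%, f = 0.5*
- Acupuncture: (0.38 + 0.62 × 0.20 × 0.19) / (1 + 0.62 × 0.20) = 0.4036/1.124 = 35.9%
- Placebo: (0.22 + 0.78 × 0.20 × 0.11) / (1 + 0.78 × 0.20) = 0.2372/1.156 = 20.5%
- Difference: 15.4 points

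*Equal shares, s = 50%, f = 0.5*
- Acupuncture: 0.4389/1.31 = 33.5%
- Placebo: 0.2629/1.39 = 18.9%
- Difference: 14.6 points

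*No repeats (s = 0), or equal success (f = 1, any s)*
- 38% against 22%, difference 16.0 points, unchanged

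*Unequal shares, 40% acupuncture and 10% placebo, f = 0.5*
- Acupuncture: (0.38 + 0.62 × 0.40 × 0.19)/1.248 = 0.4271/1.248 = 34.2%
- Placebo: (0.22 + 0.78 × 0.10 × 0.11)/1.078 = 0.2286/1.078 = 21.2%
- Difference: 13.0 points

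*The reverse, 10% acupuncture and 40% placebo, f = 0.5*
- Acupuncture: 0.3918/1.062 = 36.9%
- Placebo: 0.2543/1.312 = 19.4%
- Difference: 17.5 points

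The last two cases show that the sign of the shift depends on which arm has more repeat transfers. With equal shares, the placebo arm adds more cycles because more of its women fail (1.156 against 1.124 cycles per woman at 20%).

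**The denominator after limiting to first transfers.** A rate per first transfer still leaves out randomised women who never reach transfer. Assume 20% without a transfer in each arm: 0.80 × 38% = 30.4% and 0.80 × 22% = 17.6% per woman randomised. Power with 150 per arm is then 74%, against 86% if all 150 reached transfer at 38% and 22%. If the untransferred share differs by arm, a per-transfer rate can show a difference where none exists. With 20% pregnant per woman randomised in both arms and 20% against 30% untransferred, the per-transfer rates are 0.20/0.80 = 25.0% and 0.20/0.70 = 28.6%.

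**The case against.** The strongest reply is that the primary outcome is hardly ambiguous. The abstract, the introduction and the Primary outcome section all say first transfer. The ratio that follows can be read as the generic formula applied within that scope. The sample size counts participants, the model takes pregnancy as yes or no by group, and Table 1 has a single pregnancy-outcome visit. This stands: for the primary outcome the fault is a definition that fails to match a clear intent.

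It is also fair that entry criteria of an antral follicle count below 5 and low AMH may leave few women with spare embryos, that no sentence says later transfers are recorded or counted, and that the biochemical rate's mixed units do no harm if each woman has one transfer. All of that limits the likely size. It does not supply the missing limit in the secondary definitions. An article may leave detail to a fuller document, but here the definitions are given, and as given they count cycles.

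Three stronger readings are tempting and not supported:
- A reader might infer that the wording can move the estimate up to 19 points. That figure (42.7% against 23.7%, with repeats in 40% and 20% of failures at half success) counts any pregnancy per woman, a definition found nowhere in the article.
- A reader might infer that the acupuncture arm is bound to be pulled down. That needs more repeat transfers in that arm, which is an assumption.
- A reader might infer a general loss of power. With 120 women per arm, nominal power moves from 77.5% to 74.3% under 40%/20% shares but to 81.1% under equal 20% shares. Both figures treat correlated cycles as independent.

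**Conclusion.** The point holds in a limited form. For the primary outcome, the stated definition and Table 4 should be brought into line with the first-transfer intent stated elsewhere. For biochemical pregnancy, pregnancy loss, sustained pregnancy, live birth and implantation, nothing limits the count to the first transfer. Applied literally, they permit a unit-of-analysis error that the planned tests do not handle.

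The size is modest and rests wholly on assumed repeat transfers: 15.4 to 14.6 points instead of 16.0 for equal shares of 20–50% at half success, 13.0 points for 40% against 10%, and no change without repeats or with equal success. These figures use the primary outcome's rates as an illustration, because the article gives no planning rates for the secondary outcomes. The direction of bias is not established. The correction is worth making because it is specific and cheap, and because a denominator left open until results are seen invites selective reporting.

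**What to change.** In the Primary outcome section and Table 4:

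1. Define every pregnancy outcome on the first fresh or frozen transfer after randomisation, with at most one result per woman. Implantation keeps its embryo denominator but counts only sacs and embryos from that first transfer.
2. Use women in both parts of the biochemical rate.
3. For the primary outcome, make women randomised the main denominator, with no transfer counted as no pregnancy, in line with the intention-to-treat statement. Report the rate per first transfer as supportive. Limiting the ratio to first transfers alone would settle the repeat-transfer question but would still drop randomised women without a transfer.
4. If later transfers are of interest, report them as a separately named cumulative outcome per woman.

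The cost is wording, with no new data, and it should be done before database lock. The downsides are small: pregnancies from later transfers leave the listed rates, and rates per woman randomised are lower than rates per transfer (30.4% against 38% in the illustration with 20% untransferred), so the planning rates should be stated on the same basis.
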